## Abstract

**Background:**

In its 2006 report, *From cancer patient to cancer survivor: lost in transition*, the U.S. Institute of Medicine raised the need for a more coordinated and comprehensive care model for cancer survivors. Given the ever increasing number of cancer survivors, in general, and prostate cancer survivors, in particular, there is a need for a more sustainable model of follow-up care. Currently, patients who have completed primary treatment for localized prostate cancer are often included in a specialist-based follow-up care program. General practitioners already play a key role in providing continuous and comprehensive health care. Studies in breast and colorectal cancer suggest that general practitioners could also consider to provide survivorship care in prostate cancer. However, empirical data are needed to determine whether follow-up care of localized prostate cancer survivors by the general practitioner is a feasible alternative.

**Methods:**

This multicenter, randomized, non-inferiority study will compare specialist-based (usual care) versus general practitioner-based (intervention) follow-up care of prostate cancer survivors who have completed primary treatment (prostatectomy or radiotherapy) for localized prostate cancer. Patients are being recruited from hospitals in the Netherlands, and randomly (1:1) allocated to specialist-based (*N* = 195) or general practitioner-based (*N* = 195) follow-up care. This trial will evaluate the effectiveness of primary care-based follow-up, in comparison to usual care, in terms of adherence to the prostate cancer surveillance guideline for the timing and frequency of prostate-specific antigen assessments, the time from a biochemical recurrence to retreatment decision-making, the management of treatment-related side effects, health-related quality of life, prostate cancer-related anxiety, continuity of care, and cost-effectiveness. The outcome measures will be assessed at randomization (≤6 months after treatment), and 12, 18, and 24 months after treatment.

**Discussion:**

This multicenter, prospective, randomized study will provide empirical evidence regarding the (cost-) effectiveness of specialist-based follow-up care compared to general practitioner-based follow-up care for localized prostate cancer survivors.

**Trial registration:**

Netherlands Trial Registry, Trial NL7068 (NTR7266). Prospectively registered on 11 June 2018

## Background

In 2006, the Institute of Medicine (IOM) published a report that described the health needs of cancer survivors [1]. This report concluded that the needs of cancer survivors are not being adequately addressed. That is, survivorship care should, in addition to surveillance for recurrent disease, manage late treatment effects, address comorbid conditions, attend to psychosocial needs, and promote healthy behaviors and lifestyle. Based on this report, the IOM recommended developing new healthcare pathways for cancer survivorship. An update in 2017 concluded that we have made progress in the past decade, but still improvements are necessary to ensure comprehensive and coordinated survivorship care [2].

In addition, cancer survivorship care is facing challenges due to an increase in cancer incidence, improved detection, and improved survival rates [3]. This is particularly true for prostate cancer. In 2018, almost 450.000 men were newly diagnosed with prostate cancer in Western Europe, accounting for 22% of all new cases of cancer in males [4]. In the United States, the estimated number of new patients with prostate cancer in 2019 was 174.650 [5]. Moreover, survival rates have increased by 30% in the last 30 years in both Western Europe and the United States, resulting in a substantial increase in the number of prostate cancer survivors (5-year survival rate of 88 and 98%, respectively) [5, 6]. In the United States, there are currently over 3 million prostate cancer survivors; in the Netherlands this is about 86.000 [5, 7].

Currently in most Western countries, patients who have completed primary treatment for localized prostate cancer are often included in a specialist-based follow-up care program at the hospital. Routine follow-up care for localized prostate cancer survivors includes periodic visits to test the prostate specific antigen (PSA) [8–10]. A detectable PSA level after prostatectomy is considered a biochemical recurrence (BCR). In clinical care, BCR can (in 16–35% of cases) trigger secondary therapy for prostate cancer, including salvage local treatment or androgen deprivation therapy (ADT) [11, 12]. Managing long-term and late treatment effects and providing psychosocial support to maintain health-related quality of life (HRQOL) are also important goals of survivorship care. After primary treatment, many prostate cancer survivors experience late effects of treatment, including urinary symptoms, bowel symptoms, sexual dysfunction, symptoms related to androgen ablation, and adverse psychosocial and relationship effects [13–19].

In order to address the needs of the growing population of prostate cancer survivors in the long-term, current survivorship care models are unsustainable [1]. Different models of follow-up care for cancer patients have been proposed. There is evidence that follow-up care for cancer patients can be provided by medical specialists, general practitioners (GPs), nurses, or by sharing the care among a multidisciplinary team [20–30]. Intervention studies for chronic diseases, such as diabetes or cardiovascular disease, suggest that it is possible to coordinate follow-up between primary- and secondary care providers [31–33]. GPs, who traditionally play a crucial role in providing continuous and comprehensive care for most patients with chronic diseases, could similarly consider the role of providing follow-up care to cancer survivors. National health councils of the United States, the United Kingdom, and the Netherlands have advised giving primary health care professionals a greater role in the follow-up of cancer survivors [1, 3, 34, 35]. This is supported by evidence from randomized controlled trials of patients with breast and colorectal cancer that have shown no significant differences in adverse outcomes for patients between primary versus secondary follow-up care [23, 25–27].

There is evidence that prostate cancer patients have increased their use of primary health care 3 to 5 years after cancer diagnosis [36, 37]. Importantly, almost half (48%) of all prostate cancer patients are aged 70 years or older [38], and often have other chronic health conditions [9, 39]. A small Australian study of a shared-care follow-up model (between GPs and hospitals) for prostate cancer survivors suggests it is feasible to implement PSA testing in primary care [24].

Currently, however, there is little empirical evidence on effectiveness of prostate cancer follow-up care in primary care versus secondary care. Most of the clinical trials conducted, to date, have focused on breast and colon cancer survivors or on shared care models [23–27, 40, 41], and have typically not included an assessment of psychological morbidity and quality of life [41].

### Objectives and hypotheses

This multicenter, randomized, non-inferiority trial, the PROSPEC study, is designed to compare the (cost-) effectiveness of a GP-based versus a specialist-based follow-up care program for localized prostate cancer survivors. We hypothesize that GP-based follow-up is as effective as specialist-based follow-up care in terms of (1) adherence to the prostate surveillance guideline regarding the timing and frequency of PSA measurements; (2) the time from a BCR to prostate cancer retreatment decision-making; (3) the management of treatment-related side effects, as experienced by patients; (4) health-related quality of life and prostate cancer-related anxiety; (5) continuity of care and; (6) costs-effectiveness.

## Methods/design

### Population and setting

Prostate cancer survivors who have completed primary treatment (prostatectomy or radiotherapy) for localized prostate cancer are being recruited from 12 hospitals across different regions in the Netherlands. Eligible patients are those diagnosed with invasive prostate cancer, stage cT1a–cT3; cN0–1, cM0, pNx–pN1; R0–1, who have had a prostatectomy or have completed radiotherapy (with or without androgen deprivation therapy (ADT)) as primary treatment, and are without evidence of recurrence (PSA < 0.1 ng/ml after prostatectomy or PSA < nadir+ 2.0 ng/mL after radiotherapy). Patients are excluded from the study if: they have not completed their primary treatment less than 6 months prior to randomization; are under active surveillance; are under investigation for possible recurrence; do not have a community-based GP to provide care; are actively followed by a cancer specialist for another primary cancer; are (previously) enrolled in a study requiring ongoing follow-up by a cancer specialist; have serious (treatment-related) toxicity that requires treatment; or are unable to understand the Dutch language; or do not provide written informed consent.

### Usual care- specialist based

Men in the usual care group will receive specialist-based follow-up care according to current hospital practice as outlined in Table 1, consistent with current Dutch and European prostate cancer surveillance guidelines [10, 42].

**Table 1 Tab1:** Prostate cancer surveillance guideline [10, 42]

Surveillance	Year 1	Year 2–3	Year 4–10
Office visits	3, 6, and 12 months	Every 6 months	Annually
PSA monitoring	3, 6, and 12 months	Every 6 months	Annually
Physical examination	Only if indicated	Only if indicated	Only if indicated

### Intervention- primary care based

The intervention is based on a primary care model where localized prostate cancer survivors will be referred to their GP after the first follow-up visit at the hospital. In many western countries, as in the Netherlands, the GP is the first contact point for getting healthcare and the gatekeeper to secondary care. All patients will receive comparable follow-up care as the usual care group, as outlined in Table 1 [10, 42]. An overview of the guideline will be provided to the GP. In addition, information will be given to the GP about the patients’ primary cancer treatment, complications or treatment-related side effects (e.g. physical side effects like urinary incontinence, erectile problems, bowel problems and psychosocial problems) and the management of these side effects (e.g. pharmacological interventions, referral to a pelvic floor physiotherapist, referral to a psychologist, etc.). Information will also be given about the risk of recurrence, signs and symptoms of recurrence and recommended steps and procedures in the case of suspicion of recurrence. GPs will be asked to refer patients back to the hospital when the PSA level is > 0.2 ng/mL after surgery or > 2 ng/mL over nadir (i.e. the lowest PSA level) after radiotherapy in order to further evaluate the presence of a BCR.

### Randomization

In total, 390 consenting men will be randomized to either the GP-based (*n* = 195) or specialist-based (n = 195) follow-up care group. Randomization will be on a 1:1 ratio. The minimization technique will be applied using a randomization program (ALEA, FormVision, Abcoude, the Netherlands) to balance usual care with the intervention within a hospital on type of primary treatment (prostatectomy or radiotherapy) and clinical stage (according to the European Association of Urology (EAU) risk scores: low risk; intermediate risk; high risk [10]). Blinding of participants and clinicians is not possible due to the nature of the intervention.

### Recruitment

We are recruiting patients from academic and general hospitals in the Netherlands. Medical specialists are asked to identify eligible patients at the first follow-up visit after primary treatment has been completed. Eligible patients are invited to participate in the study and, if interested, receive the information letter of the study. One week after the invitation, patients are contacted by telephone to explain the GP-based follow-up care and the RCT, and to confirm their willingness to participate in the study. After a patient has indicated his willingness to participate, his GP is contacted by telephone and asked whether (s)he is willing to participate in the study. If a GP declines participation, the patient cannot be included in the study and will be personally informed by telephone. Consenting patients will be randomized to specialist-based (usual care) or GP-based (intervention) follow-up care. Figure 1 details the study flow chart.

**Fig. 1 Fig1:**
[figure not shown]
Study flow chart. First follow-up visit is ≤6 months post-treatment. T0 = measurement prior to randomization; T1 = measurement 12 months post-treatment, T2 = measurement 18 months post-treatment, T3 = measurement 24 months post-treatment. Abbreviations: GP = General Practitioner

All participants will be followed during a 2-year study period. Patients allocated to GP-based follow-up may be referred back to the hospital at any time during the study. Similarly, patients allocated to specialist-based follow-up are free to consult their GP any time during the study. Patient recruitment and data collection for this trial started in July 2018.

### Data collection

Data are collected prior to randomization (T0), and at 12 (T1), 18 (T2), and 24 (T3) months after primary treatment has ended. The primary outcome is being abstracted from the medical records of participating hospitals and primary care practices. Secondary outcomes are also being abstracted from the medical records and collected using validated questionnaires. A reminder is sent to participants who do not return the questionnaire within 2 weeks. If a participant does not complete the questionnaire 2 weeks after the reminder, he will be contacted by telephone.

### Study outcomes

#### Primary study outcome

Adherence to the prostate cancer surveillance guideline is assessed on the basis of the timing and frequency of PSA measurements (Table 1) and will be assessed at T0, T1 and T3. A detailed description of the outcome measures are provided in Table 2.

**Table 2 Tab2:** Outcome measures

Description of outcome	Assessment	Description of measure
Sociodemographic and clinical data	Sociodemographic data, disease and treatment characteristics will be abstracted from medical records or reported by the patient.	Patient reported: place of birth, marital status, educational level, employment, lifestyle factors (i.e. smoking, alcohol consumption, length and weight), and the self-administered comorbidity questionnaire [43].
		Medical records: birth-month and year, hospital where primary treatment took place, referred specialist, date of diagnosis, date and type of treatment, tumor characteristics (clinical and pathological stage).
**Primary outcome**		
Adherence to the prostate cancer surveillance guideline (Table 1)	PSA measurements	Number of PSA measurements will be abstracted from medical records.
**Secondary outcomes**		
The time from a BCR to prostate cancer retreatment decision-making	PSA value and referrals	The time from any detectable PSA level (> 0.2 ng/mL after surgery, > 2.0 ng/mL over nadir after radiotherapy) to the decision of prostate cancer retreatment in the hospital.
The management of treatment-related side effects	Assessment of Patients’ Experience of Cancer Care (APECC) survey [44]	37 items, organized into 10 scales in the following six areas: access to care; interaction with physicians; interaction with other members of the health care team; discussion of health promotion; perceptions of coordination of care; and the management of treatment-related side effects.
Health-related quality of life	EORTC Quality of Life Questionnaire Core 30 (QLQ-C30) [45]	30 items, organized into 5 functional scales (physical, role, emotional, cognitive, social), 3 symptom scales (pain, fatigue, and emesis), 6 items (dyspnea, sleep disturbance, appetite loss, constipation, diarrhea, and financial impact), and an overall QL scale.
Prostate cancer-related quality of life	EORTC Prostate cancer specific module (PR25) [46]	25 items, organized into 5 scales (urinary symptoms, bowel symptoms, hormonal treatment-related symptoms, sexual activity, and sexual functioning) and one item (incontinence aid).
Prostate cancer-related anxiety	Memorial Anxiety Scale of Prostate Cancer (MAX-PC) [47, 48]	18 items, organized into one scale consisting of 3 subscales (general prostate cancer anxiety, anxiety related to PSA levels in particular, and fear of recurrence).
Continuity of care	Nijmegen Continuity Questionnaire (NCQ) [49]	28 items, organized into one scale consisting of 3 subscales (personal continuity, care provider knows me and shows commitment, and team/cross-boundary continuity).
Cost-effectiveness	EuroQol 5-Dimension (EQ-5D-5L) [50]	5 items (dimensions) multi-attribute utility questionnaire that measures mobility, self-care, usual activities, pain/discomfort and anxiety/depression in 5 levels.
	Health care costs	Medical activities abstracted from the management systems of the hospitals and GP practices
	Indirect costs	Patient reported productivity losses [51], medical consumption [52] and travel costs

*Abbreviations*: *PSA* Prostate Specific Antigen, *BCR* Biochemical Recurrence, *EORTC* European Organization for Research and Treatment of Cancer, *QL* Quality of Life, *GP* General Practitioner

#### Secondary study outcomes

The time from a BCR to prostate cancer retreatment decision-making will be assessed at T0, T1 and T3. This is defined as the time from a rising PSA level after surgery (> 0.2 ng/mL) with or without radiotherapy or a rising PSA level of 2 ng/mL over the post-treatment nadir after radiotherapy to the decision regarding prostate cancer retreatment.

Other secondary outcome measures will assess the self-reported management of treatment-related side effects, health-related quality of life, prostate cancer-related quality of life, prostate cancer-related anxiety, and cost-effectiveness as described in Table 2. They will be assessed at T0, T1, T2, and T3 time points. Perceived continuity of care will be assessed in the T2 questionnaire.

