#### Patient-reported outcomes

For the patient-reported outcomes (e.g. HRQOL, prostate-specific anxiety, etc.) we will compare changes in mean questionnaire scores over time between the usual care and the intervention group. Based on 390 patients and a survey attrition of 20%, power is at least 80% to detect a difference in questionnaire-based outcomes between patients who had their follow-up at their GP or specialist with an effect size of 0.1, at a two sided-significance level of 5%. With this sample size we will be able to detect clinically meaningful differences [53].

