#### Secondary study outcomes

For patients treated with prostatectomy, time from a BCR to prostate cancer retreatment decision-making will be evaluated by Kaplan-Meier methods including log-rank tests as well as multivariable Cox proportional hazards regression. Non-proportionality of hazards will be assessed by Schoenfeld residuals. In exploratory analyses, we will perform subgroup analyses by patient characteristics (e.g.: clinical stage: ≤ cT2b-c or cT3).

Scores for the APECC, EORTC QLQ-C30 and QLQ-PR25, MAX-PC, NCQ, EQ-5D-5L questionnaires will be calculated according to published scoring algorithms. Between-group differences over time in mean scores will be tested using a mixed effects modelling approach. For the moderation analysis, a regression based model will be constructed for each potential moderator separately in order to estimate the conditional (interaction) effect. Standardized effect sizes will be calculated by dividing the difference in mean change scores from baseline to follow-up between groups by the pooled baseline standard deviation.

The cost-effectiveness analysis will compare the costs and health benefits between both groups. This comparison is typically expressed in incremental cost, − health effects (often quality-adjusted life-years or QALYs), and - cost-effectiveness ratio (ICER) (e.g., incremental cost per QALY gained). A societal perspective from the Netherlands, plus lifelong time horizon will be adopted, according to the Dutch guidelines [54]. A trial-based analysis will be combined with a Markov decision analytic model, in order to capture both the trial endpoints at 2 years follow-up as well as the life long time horizon. Using a monthly cycle length, the model will simulate the lifelong course of events in a hypothetical cohort of prostate cancer survivors. We will include the estimation of the degree of uncertainty about each input parameter and the use of (probabilistic) sensitivity analyses. We will apply the most relevant severity-based ceiling ratio between €20,000 and €80,000 per QALY [55]. If necessary, Value of Information (VOI) analysis will be performed to support decision-making regarding adoption and further research [56].

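### The Nijmegen Continuity Questionnaire (NCQ) is collected once, at 18 months, but the only analysis, effect size and power figure given for questionnaires need repeated scores.

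*Protocol article*

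**What the plan says.** All of this is in the protocol article.

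- **Schedule** (Study outcomes, Secondary study outcomes). Of the patient-reported outcomes other than continuity of care, the article says "They will be assessed at T0, T1, T2, and T3 time points". Continuity of care has its own sentence: "Perceived continuity of care will be assessed in the T2 questionnaire". The legend to Fig. 1 fixes the time: "T2 = measurement 18 months post-treatment".
- **Analysis** (Data analysis, Secondary study outcomes). The NCQ appears in the scoring sentence: "Scores for the APECC, EORTC QLQ-C30 and QLQ-PR25, MAX-PC, NCQ, EQ-5D-5L questionnaires will be calculated according to published scoring algorithms". The next sentence reads "Between-group differences over time in mean scores will be tested using a mixed effects modelling approach". Standardised effect sizes are then obtained by "dividing the difference in mean change scores from baseline to follow-up between groups by the pooled baseline standard deviation". No other analysis is given for the NCQ.
- **Power** (Power calculation, Patient-reported outcomes). The comparison is described as one of changes in mean scores over time. With 390 patients and 20% survey attrition, "power is at least 80% to detect a difference in questionnaire-based outcomes" at an effect size of 0.1, two-sided 5%. No questionnaire is excepted.
- **Hypothesis** (Objectives and hypotheses). Continuity of care is item 5 of the outcomes on which GP-based care is hypothesised to be as effective as specialist-based care.

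**The concern.** The schedule and the analysis do not fit each other. A single NCQ score per man gives no baseline value, no change score, no baseline SD and no time dimension. The described model and effect size therefore cannot be produced for this outcome, and the article names nothing in their place. The method actually used would have to be chosen later, possibly with the data in view.

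The power statement adds to this. It rests on change over time, and taken at face value it tells the reader that the trial is sensitive to a small NCQ difference. The hypothesis is one of equal effectiveness, and the Discussion restates it as an expectation of no significant difference. A non-significant T2 result could then be taken as support for GP-based care when the comparison has much less power than stated.

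**Working it through.** **Inputs.** 390 men, 195 per arm, 20% survey attrition, effect size 0.1, two-sided 5%, power at least 80% (Power calculation). One NCQ assessment, at T2. The article does not say which kind of effect size 0.1 is, so both usual readings are taken. It gives no correlation between repeated scores, so ρ below is an assumption shown over a range.

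**Step 1: men with a T2 score.** 195 × 0.80 = 156 per arm, 312 in all.

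**Step 2: can the plan's own figure be reproduced?**

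*Reading A, 0.1 as Cohen's f for a group-by-time interaction over four time points.* The noncentrality is λ = f² × N × m / (1 − ρ), with m = 4 and 3 and 930 degrees of freedom.

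- ρ = 0: λ = 0.01 × 312 × 4 = 12.48, power 85%.
- ρ = 0.5: λ = 24.96, power 99%.

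This agrees with the stated 80% or more, but it needs repeated measurements.

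*Reading B, 0.1 as a standardised mean difference d, analysed as a change score.* The SD of change is √(2(1 − ρ)) in units of the score SD. With 156 per arm:

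| Assumed ρ | Power at d = 0.1 |
|---|---|
| 0.5 | 14% |
| 0.8 | 29% |
| 0.9 | 51% |
| 0.95 | 80% |

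This reaches the stated figure only at ρ of about 0.95, and it too needs a baseline score.

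The normal approximation used in Step 3 reproduces the article's other two powers: 86.3% for the non-inferiority comparison (135 per arm, 90% adherence in both arms, margin 10 points, one-sided 5%; stated 86%) and 80.2% for the APECC comparison (60 per arm, 8.1 points, SD 15.8; stated 80%).

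**Step 3: a single T2 comparison, 156 per arm.** The standard error in SD units is √(2/156) = 0.1132.

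- d = 0.1: Φ(0.1/0.1132 − 1.96) = Φ(−1.08) = 14%.
- f = 0.1, which for two equal groups is d = 2f = 0.2: Φ(0.2/0.1132 − 1.96) = Φ(−0.19) = 42%.
- Difference detectable with 80% power: (1.960 + 0.842) × 0.1132 = 0.32 SD.
- Half-width of the 95% confidence interval: 1.96 × 0.1132 = 0.22 SD.

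**Step 4: no attrition, 195 per arm.** The standard error is √(2/195) = 0.1013. The detectable difference is 2.802 × 0.1013 = 0.28 SD, and power at d = 0.1 is 17%.

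**Step 5: size needed.** For 80% power at d = 0.1 with one assessment: 2 × 2.802² / 0.1² ≈ 1,570 evaluable men per arm.

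**The case against.** The NCQ is named only in the sentence on scoring. The mixed-model and effect-size sentences name no instrument, and the power paragraph gives quality of life and anxiety as examples and speaks of changes over time. On that view both were meant for the repeated questionnaires, and a condensed article may leave the handling of a single-assessment outcome to the analysis plan.

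Part of this stands: the NCQ falls under those sentences by natural reading, not by name. But the article does not leave the matter open. It lists the NCQ with the others, follows the list directly with one analysis, and makes no exception there or in the power statement.

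Three stronger inferences are tempting, and the article does not support them:

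- **That the detectable difference is three times the claimed one.** The ratio 0.32/0.1 = 3.2 holds only if 0.1 is a standardised mean difference. If it is Cohen's f, the ratio is 0.32/0.2 = 1.6. The effect size defined in the data analysis section favours the first reading, but the power paragraph does not say.
- **That the trial can exclude only differences beyond 0.32 SD.** That figure is what can be detected with 80% power. What is excluded depends on the confidence interval, about 0.22 SD either side of the observed difference.
- **That continuity of care cannot be analysed at all.** The arms are randomised, so a comparison of T2 scores is valid without a baseline.

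**Conclusion.** The point holds as an inconsistency in the described analysis and power for one secondary outcome. The over-time model and the baseline-standardised change cannot be computed for an outcome assessed once. The stated power of at least 80% at effect size 0.1 fails for the NCQ on both readings: 14% as a standardised mean difference, 42% as Cohen's f. The difference detectable with 80% power is about 0.32 SD with 20% attrition and 0.28 SD with none.

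These figures assume equal arms, attrition at T2 equal to the stated 20%, and an unadjusted comparison of means. The primary outcome and the trial's sample size are not affected. Whether 0.1 is realistic for the repeatedly measured questionnaires is a separate question and adds no weight here.

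**What to change.** 1. In Data analysis, take the NCQ out of the text on differences over time and change from baseline. State instead that T2 NCQ scores are compared between arms by linear regression adjusted for the minimisation factors (hospital, primary treatment, risk group), with the effect size standardised by the pooled T2 SD.
2. In Power calculation, except the NCQ from the statement on questionnaire-based outcomes and give its detectable difference as about 0.32 SD (80% power, two-sided 5%, 156 per arm).
3. State that the NCQ difference will be reported with its 95% confidence interval, expected half-width about 0.22 SD, and that a non-significant result will not by itself be read as equal effectiveness.

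The cost is a few sentences and one restated figure, with no new data. Adding an NCQ assessment at T3 would not solve the problem, because it supplies no baseline and the change-from-baseline effect size would still be impossible.
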